## Methods/Design

### Study Design

The study will employ a cluster randomised controlled trial design (see Figure 1). A sample of eligible long day care services in the study region will be randomly selected and approached to participate in the trial. Ten services will be randomly allocated to a service-level physical activity intervention, delivered over a 15 week period, and ten services will be allocated to a wait list control group. The primary trial outcome measure, mean child step counts per minute, will be collected at baseline and approximately 6 months following baseline data collection. Services allocated to the wait list control group will receive the intervention after the collection of all follow-up data.

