### Random allocation of long day care services

Services will be allocated to either the intervention or control condition using block randomization performed in a 1:1 ratio in randomly sequenced blocks of two, four or six by a computerized random number function in Microsoft Excel. Allocation of services will be undertaken by a statistician who will have no other involvement in the study, and will occur after all services have been recruited into the trial. As evidence suggests physical activity practices in long day care services differ according to the socio-economic status of the area in which the service is located [26], the random allocation of long day care services will be stratified by the socioeconomic characteristics (high/low) of the service locality. Long day care services with a postcode ranked in the top 50% of New South Wales, based on the Socio-Economic Indexes for Areas [27] will be defined as a 'high socio-economic area service' and those with a postcode ranked in the lower 50% will be defined as a 'low socio-economic area service'. Due to the difficulty in blinding services to their group allocation, this trial will be an 'open' trial. After services have consented to participate in the study a member of the research team not involved in recruitment or data collection will inform services of the group to which they were allocated.

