#### Parent and child demographics and physical activity

Parents will be asked to report child age, Aboriginal and/or Torres Strait Islander status, gender, postcode of residence and parental education level on the participant consent form. Parents will also be asked about the usual number of days their child spends at long day care each week and the usual amount of time their child spends being physically active and participating in small screen recreation during weekdays outside of care hours. Items assessing demographic and time spent in physical activity and small screen recreation outside of care were based on those used in other population based surveys of pre-school age Australian children [60].

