### Sample size and power calculations

Assuming a step count per minute of 17 among children attending control services and an intra-class correlation of 0.1 [62] a sample size of approximately 280 children (140 per group) attending 20 services at the 6 month follow-up will be sufficient to detect a difference between intervention and control groups of 4 steps per minute with 80% power at the 0.05 significance level. Assuming that long day care services care for 30 children aged three to five years per day on average, a study participation rate of 65% will be required to obtain the desired sample given a 20% attrition rate at the follow-up assessments.

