### Analysis

All statistical analyses will be performed with SAS (version 9.2 or later) statistical software. All statistical tests will be two tailed with an alpha value of 0.5. Descriptive statistics will be performed to describe the demographic and service characteristics of intervention and control groups at baseline. Similarly measures of intervention implementation will be described using descriptive statistics.

The effectiveness of the intervention on child physical activity will be assessed utilising an intention to treat approach. An intention to treat analysis includes all participants in the analysis based on the groups to which they were allocated, without excluding data based on missing outcomes or non-adherence [22]. Specifically, linear mixed models will be used to examine between group differences on the primary trial outcome. Such analyses account for the correlation between pre and post measures and adjust for clustering. Any differences in the characteristics of participants at baseline will be adjusted for in the final linear model.

To ensure the results are robust, a sensitivity analysis will be performed whereby participants' observations at baseline will be used as a substitute for any subsequent missing data. A per-protocol analysis will also be conducted with participants from services which have sufficiently implemented the intervention.

Acceptability of the intervention among staff of services will be assessed by collapsing Likert scale categories and reporting the percentage of staff who responded 'strongly agree' or 'agree' to each acceptability item.

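### The primary model's extra covariates are chosen by observed baseline differences, with no list or criterion, so the model is not fixed in advance

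*Protocol article*

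**What the plan says.** In the protocol article, Analysis, "linear mixed models will be used to examine between group differences on the primary trial outcome". The next sentence adds: "Such analyses account for the correlation between pre and post measures and adjust for clustering". The paragraph then closes with the covariate rule: "Any differences in the characteristics of participants at baseline will be adjusted for in the final linear model".

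The candidates appear under Measures, in the part on parent and child demographics: "Parents will be asked to report child age, Aboriginal and/or Torres Strait Islander status, gender, postcode of residence and parental education level". The same part adds usual days in care, and activity and screen time outside care. Study Design confirms that the outcome itself is measured before the intervention: "mean child step counts per minute, will be collected at baseline and approximately 6 months following baseline data collection".

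The section on random allocation uses "block randomization performed in a 1:1 ratio in randomly sequenced blocks of two, four or six" and says that the allocation "will be stratified by the socioeconomic characteristics (high/low) of the service locality". The Analysis section does not name that stratum as a model term.

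**The concern.** The covariate sentence is a positive instruction for the primary model, so it is not merely detail left to a fuller document. It makes inclusion depend on how the groups happen to compare at baseline. Three things follow.

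- **The model is unknown until the data are seen.** Which characteristics are eligible and how large a difference must be are both open, so two analysts could follow the sentence and fit different primary models.
- **The criterion is the wrong one.** An observed imbalance says nothing about whether a characteristic predicts step counts. The rule can omit a balanced predictor and admit an unbalanced characteristic that is irrelevant.
- **The design variable is left out.** The stratum belongs to the service locality, whereas the rule speaks of participants. Stratification also makes the stratum unlikely to differ between groups. Read literally, the rule would seldom or never bring it in.

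At stake are the reproducibility of the primary estimate and some precision.

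**Working it through.** **Inputs from the article.** Ten against ten services, and 280 children at follow-up, so 280/20 = 14 per service. The sample size section states: "Assuming a step count per minute of 17 among children attending control services and an intra-class correlation of 0.1". It gives no standard deviation, so the 280 cannot be reproduced. Solving backwards, the design effect is 1 + 13 × 0.1 = 2.3 and the effective size is 140/2.3 = 60.9 per arm. The implied SD is 4 × √(60.9/2)/(1.960 + 0.842) ≈ 7.9 steps per minute. Nothing below depends on this SD.

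**Assumptions, none given in the article.** Five candidate characteristics with intra-class correlation 0.05; a baseline to follow-up correlation r of 0.3, 0.5 or 0.7; a slope of 0.1 or 0.2 SD for each characteristic; and selection by a baseline test at p < 0.05 or p < 0.20.

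**1. How often does chance alter the model?** With a valid 5% test of five independent characteristics, at least one is flagged with probability 1 − 0.95^5 = 0.23. At a 0.20 cut it is 1 − 0.80^5 = 0.67.

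A child-level test that ignores clustering flags more. The characteristic's design effect is 1 + 13 × 0.05 = 1.65, so the 5% test really cuts at 1.960/√1.65 = 1.526, a two-sided tail of 0.127. Then 1 − 0.873^5 = 0.49. At a 0.20 cut, 1.282/√1.65 = 0.998 gives a tail of 0.318, and 1 − 0.682^5 = 0.85. Simulation (2,000 runs per scenario) agreed: 0.49-0.50 and 0.86.

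**2. What does selection cost in precision?** The simulation used 20 services of 14 children with intra-class correlation 0.1. Baseline steps entered as a covariate, with selection at p < 0.05. Entries are the variance of the group effect relative to no adjustment at all.

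| r | slope | baseline only | baseline + selected | baseline + all five | selected ÷ all five |
|---|---|---|---|---|---|
| 0.3 | 0.1 | 0.904 | 0.894 | 0.886 | 1.01 |
| 0.3 | 0.2 | 0.902 | 0.839 | 0.775 | 1.08 |
| 0.5 | 0.1 | 0.747 | 0.739 | 0.729 | 1.01 |
| 0.5 | 0.2 | 0.755 | 0.717 | 0.654 | 1.10 |
| 0.7 | 0.1 | 0.528 | 0.514 | 0.500 | 1.03 |
| 0.7 | 0.2 | 0.564 | 0.512 | 0.448 | 1.14 |

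The variance penalty is about 1-14%. At worst the standard error is √1.143 = 1.07 times as large. The share of the full gain that is kept runs from (1 − 0.839)/(1 − 0.775) = 0.72 to (1 − 0.514)/(1 − 0.500) = 0.97. In the simulation the characteristics affect follow-up but not baseline steps. If they affected both, the baseline count would carry part of their contribution, so the upper end probably overstates the loss.

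**3. Does it inflate false positives?** At nominal 0.05, the selected model rejected in 0.021-0.041 of null runs and the model with all five in 0.029-0.044 (Monte Carlo standard error about √(0.03 × 0.97/2000) = 0.004). Part of the shortfall from 0.05 is common to both and comes from the testing method used. Selection lowered the rate further, clearly so only in some of the scenarios with slope 0.2. No inflation appears.

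**The case against.** **The baseline outcome is already in the model.** This stands. The sentence on pre and post measures applies whatever imbalance is seen. A reader might infer that the rule forfeits most of the precision available from adjustment. The documents do not support that: it would be true only if baseline steps were absent from the model. Likewise, a large power loss appears only if one assumes a strong predictor that is not otherwise modelled and compares against an unadjusted analysis. The article gives no such predictor and plans no such analysis.

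**The printed alpha of 0.5.** A reader might apply it to baseline comparisons and conclude that half of all characteristics would be flagged. The article plans only descriptive statistics at baseline and states no test there. The sample size section uses 0.05, so the 0.5 is a separate inconsistency with no weight here.

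**Not every imbalance need be chance.** Services are randomised, not children. The trial is open, and the article does not say that parental consent precedes disclosure of allocation. Differences in who takes part could therefore be real, which gives adjustment some rationale. This stands in part: it supports a supplementary analysis, but a fixed list still serves the primary model better.

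**A covariate list may sit in a fuller document.** Its absence from an article is not the point. The point is the selection rule that the article does state.

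**Conclusion.** The point holds in a limited form. The rule leaves the primary model's additional covariates open until the data are seen, chooses them on an uninformative criterion, and does not name the stratification factor. That conclusion needs no assumed figures.

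The size does rest on assumptions. The precision loss is about 1-14% in variance for r of 0.3-0.7, slopes of 0.1-0.2 SD and a 0.05 cut. It also assumes that the mixed model uses baseline steps as a covariate would. The article does not give the parameterisation. A group-by-time model with unconstrained baseline means would behave like a change-score analysis, with variance factor 2(1 − r), that is 1.4, 1.0 and 0.6 at r = 0.3, 0.5 and 0.7. That is a separate matter from covariate selection.

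A reader might infer an inflated type I error. Under a mechanical rule the test is, if anything, somewhat conservative. An undefined criterion does leave room for discretion, but nothing in the article suggests that it would be used selectively. The change is worth making because it is nearly free, not because the trial's conclusion is at serious risk.

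**What to change.** Replace the covariate sentence with: *The primary model will include baseline steps per minute, the SES stratum, child age and sex, irrespective of observed baseline balance.* Keep any adjustment prompted by observed imbalance as a supplementary analysis, labelled as such, with the characteristics and the criterion stated.

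The cost is one sentence. All four variables are already collected or used in the allocation, and no sample size, visit or procedure changes. The stratum uses one service-level degree of freedom (18 to 17 with 20 services). The primary model would not adjust for an imbalance in an unlisted characteristic; the supplementary analysis covers that.

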## Discussion

There is a clear need for intervention studies to extend research regarding the effectiveness of interventions to increase physical activity behaviours of young children attending childcare [17]. This trial aims to advance the currently limited experimental evidence in this field and will contribute important information regarding the effectiveness, feasibility and acceptability of comprehensive service based strategies to address physical activity at childcare. Strengths of this study include the trials randomised design, the use of theory and multi-disciplinary input into the intervention design, the implementation of the intervention by usual service staff, and the use of an objective measure of physical activity.

## Conclusion

This manuscript provides a description of the implementation of a cluster randomised controlled trial of a multi-component intervention aimed at increasing physical activity levels of preschool aged children attending long day care services. The study is one of a handful of randomised trials of such interventions internationally and will contribute greatly to the evidence regarding the effectiveness of strategies in this setting.
